## Objectives

### Primary objective

This study aimed to evaluate the effectiveness of a home-based inspiratory muscle training (IMT) protocol compared to an IMT SHAM group for improving respiratory muscle strength, dyspnea, and quality of life of post-COVID-19 patients.

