## Material and methods

### Type of study and location of research

This randomized, controlled, double-blind, parallel, two arm clinical trial will be conducted at the Instituto de Medicina Tropical and of Universidade Federal do Rio Grande do Norte, referred from the ambulatory of infectology of Hospital Giselda Trigueiro (Rio Grande do Norte, Brazil) will be recruited.

Sample size will be determined using maximal inspiratory pressure (MIP) (GPower Software version 3.1.9.2, Kiel, Germany) after a pilot study with five patients in each group (total of 10 patients). Mean and standard deviation will be used to estimate effect size, and a bilateral distribution with alpha error of 0.05 and 80% power will be adopted. Sample size will be adjusted assuming a dropout rate of 20%.

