### Interventions

Patients included will be evaluated in three moments: pre-training (initial), post-training (six weeks after pre-training), and retention (24 weeks after pre-training). After recruitment, one researcher previously trained and blinded to allocation will evaluate vital signs, anthropometric measurements, pulmonary volume, respiratory muscle strength, handgrip strength, quality of life, anxiety, depression, functional status, and functional capacity.

After initial evaluation, all patients will receive a POWERbreathe® (POWERbreathe®, HaB Ltd, Southam, UK) device and be individually oriented on how to perform the IMT protocol. An experimental session will be conducted for familiarization with the device. Patients will receive a phone call every three days from the second researcher (who will not participate in the evaluation) to confirm if IMT is being performed correctly and resolve doubts regarding the protocol. At the end of each week, patients from EG will receive a video call from the second researcher to adjust load of the device.

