#### Dyspnea

Dyspnea will be assessed using the Medical Research Council scale adapted to Portuguese. Patients must indicate the impact of dyspnea on mobility during daily activities. Scores range between 1 and 5, and highest values indicate greater dyspnea [17].

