### Statistical analysis

SPSS software version 22.0 (IBM Corp. USA) will be used for data analysis. Normality will be verified using Shapiro-Wilk or Kolmogorov-Smirnov, according to the number of patients included. Variables presenting nonparametric distribution will be compared using Wilcoxon (intragroup analysis) and Mann-Whitney test (intergroup analysis), whereas repeated measures two-way ANOVA will be performed in case of parametric distribution. Dunn’s post hoc test will be used to identify significant differences in the two-way ANOVA test.

Descriptive analyses will be conducted using mean and standard deviation or median and interquartile range (25% - 75%), according to data distribution. A significance level of 5% will be applied to minimize type I error. The power of the study and effect size will also be performed for the main results of the study.

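### A normality test chooses the analysis for each variable, and the nonparametric branch specifies no between-arm test of change and no baseline adjustment

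*Protocol article*

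**What the plan says.** The Statistical analysis section, repeated in the Abstract, sets the method in two steps.

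- The selector: "Normality will be verified using Shapiro-Wilk or Kolmogorov-Smirnov, according to the number of patients included".
- If normality fails: "Variables presenting nonparametric distribution will be compared using Wilcoxon (intragroup analysis) and Mann-Whitney test (intergroup analysis". If it holds: "whereas repeated measures two-way ANOVA will be performed in case of parametric distribution".

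The surrounding design is as follows.

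- Primary objective: active training "compared to an IMT SHAM group for improving respiratory muscle strength, dyspnea, and quality of life of post-COVID-19 patients".
- Visits (Interventions section): "Patients included will be evaluated in three moments: pre-training (initial), post-training (six weeks after pre-training), and retention (24 weeks after pre-training".
- Dyspnea, one of the primary outcomes: "Scores range between 1 and 5, and highest values indicate greater dyspnea".
- Sample size: "a bilateral distribution with alpha error of 0.05 and 80% power will be adopted", and "Sample size will be adjusted assuming a dropout rate of 20" per cent. The effect size and SD are to come from a pilot of five patients per arm, so no N, effect or SD is given.

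For the nonparametric branch the text does not say which quantity enters the Mann-Whitney test (follow-up value or change) or how baseline is used. It does not say which of the two tests decides efficacy.

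**The concern.** The trial asks whether active training does better than sham. A plan for that question should fix in advance one between-arm comparison per outcome, and should use baseline, which every patient has.

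Three features of the written plan fall short.

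1. The method depends on a test of the data it will analyse, so the estimand and test for a primary outcome are unknown until the data are in.
2. In the nonparametric branch, the only test that certainly uses baseline is the Wilcoxon test, which compares an arm with itself and handles two of the three visits at a time. The input to the between-arm test is open, so follow-up values or change could be chosen after the results are seen.
3. In the parametric branch, the standard SPSS repeated measures ANOVA keeps only patients with all three visits. A patient who misses only week 24 would also lose the week-6 result.

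At stake are power, and the room left for a claim of benefit built on within-arm results. Patients are selected for reduced respiratory muscle strength and are recovering from an infection, so some improvement in both arms is plausible.

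**Working it through.** The protocol states no figure to reproduce. Everything below is illustrative: two-sided alpha of 0.05 is from the protocol, while N, effect size, correlation and distribution are assumptions.

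**Which branch dyspnea enters.** Shapiro-Wilk was simulated on several assumed five-level distributions. At n = 30 it rejected normality in essentially every sample. At n = 20 it rejected in roughly 65% to 95%, depending on the distribution. So the nonparametric branch is probable for this scale, and near certain from about 30 observations.

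**Power of a between-arm test.** Assume n = 30 per arm, true effect 0.6 SD, normal data and baseline correlation ρ. Approximate power is Φ(0.6 × √(30/2) / s − 1.96), where 0.6 × √15 = 2.324 and s is the relative SD:

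- Mann-Whitney on follow-up: s = 1/√(3/π) = 1/0.977, so Φ(2.271 − 1.96) = Φ(0.311) = 62%.
- Change score: s = √(2(1 − ρ)).
- ANCOVA: s = √(1 − ρ²). At ρ = 0.5, Φ(2.324/0.866 − 1.96) = Φ(0.723) = 77%. At ρ = 0.7, Φ(2.324/0.714 − 1.96) = Φ(1.294) = 90%.

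Simulation (4,000 trials per setting) gives values slightly below these approximations:

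| ρ | Mann-Whitney, follow-up | change score | ANCOVA |
|---|---|---|---|
| 0.3 | about 60% | about 49% | about 66% |
| 0.5 | about 60% | about 62–64% | about 75–76% |
| 0.7 | about 60% | about 82–85% | about 88–89% |

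The open choice between follow-up and change therefore matters in both directions: change is worse at ρ = 0.3 and much better at ρ = 0.7. ANCOVA is best in every row.

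**Skewed data**, since this branch is meant for non-normal variables. Lognormal, 26 per arm, effect 0.8 SD on the log scale, ρ = 0.5 / 0.7 / 0.8:

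- Mann-Whitney on follow-up: 78% / 78% / 78%
- Mann-Whitney on change: 80% / 95% / 99%
- rank ANCOVA: 87% / 96% / 99%

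With no treatment difference, all three between-arm tests rejected in 4.3% to 5.5% of trials, so their size is correct.

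**In patients.** For an assumed effect of 0.8 SD and 80% power, follow-up values alone need 25 per arm. Baseline adjustment needs 19 at ρ = 0.5 and 13 at ρ = 0.7.

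**Reading the within-arm tests as evidence.** Assume both arms truly improve by 0.4 SD of change, 30 per arm. The chance p that one arm's Wilcoxon test is significant is approximately Φ(0.4 × √30 × 0.977 − 1.96) = Φ(0.181) = 57%; simulation gives 54%. With p = 0.54:

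- active arm significant and sham not: p(1 − p) = 0.54 × 0.46 = 25%
- exactly one arm significant: 2p(1 − p) = 50%

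Since p(1 − p) cannot exceed 0.25, this setting is close to the worst case. In the skewed-data simulation at 26 per arm, with equal improvement of 0.3 or 0.5 SD of the outcome on the log scale, active-only significance occurred in 4% to 25% of trials.

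**Parametric branch.** With 20% dropout, the share of patients whose known week-6 value is lost runs from 0% (all leave before week 6) to 20% (all leave after it). For an assumed 60 patients enrolled, that is 0 to 12. The protocol gives no timing.

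**The case against.** A reader might infer that the nonparametric branch never tests whether change differs between arms, discards baseline, and would declare benefit when both arms improve equally. The documents do not support that.

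- The text names a Mann-Whitney test for the between-arm analysis without saying that it is run visit by visit or on raw values. Run on change scores, it would test differential change and use baseline.
- Even on follow-up values alone, Mann-Whitney is a valid comparison in a randomised trial. The error rates above confirm this; the cost is power.
- No stated rule declares benefit from a significant Wilcoxon test in one arm. The tests are labelled as within-arm and the objective is comparative, so the 25% figure describes a misreading that the plan leaves open, not the plan's own error rate.
- Repeated measures ANOVA can carry a group-by-time term, which does test differential change. Maximal inspiratory pressure is continuous and may well go down this branch.
- Loss of incomplete patients follows from the usual SPSS procedure. The protocol names the software but not the procedure, and missing-data handling is often left to a SAP.

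All of this stands. It does not remove the core point: the article fixes a data-dependent choice of method, and for a primary outcome it probably leads to a branch with no specified baseline adjustment, no specified test of change and no stated deciding test. The normality selector is stated outright, so it is not a detail deferred to a SAP.

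**Conclusion.** The point holds as a matter of specification and efficiency, not as a failure of validity. The method for each variable hangs on a normality test, and the nonparametric branch leaves the decisive between-arm analysis underspecified. Under the assumed inputs, follow-up-only Mann-Whitney gives up about 16 percentage points of power against ANCOVA at a correlation of 0.5 (60% against 76%) and about 29 at 0.7 (60% against 89%). At 0.3 the loss is only about 6 points, so its size depends on a correlation that the protocol does not give. The risk of about 25% for a misleading active-only result applies only if within-arm tests are taken as evidence of efficacy. The loss of week-6 data in the ANOVA branch lies between 0% and 20% of patients.

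**What to change.** Remove the normality test as selector and prespecify one baseline-adjusted between-arm analysis per outcome.

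- **Continuous outcomes:** ANCOVA, or a linear mixed model on the two post-baseline visits with group, visit, group-by-visit and the baseline value as covariate, using all available data. SPSS can fit this. Check residuals, not raw values.
- **Dyspnea and functional status scales:** ordinal regression adjusted for baseline, or rank ANCOVA.
- **Deciding result:** state that the adjusted between-arm difference at the post-training visit, with its 95% confidence interval, decides efficacy. For an ordinal model, this is the adjusted between-arm effect with its interval.
- **Within-arm tests:** descriptive only.

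Which of the three primary outcomes ranks first is a separate issue that this change does not settle.

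The cost is a few sentences of analysis text and slightly more programming. Baseline values are already collected, so no new data or visits are needed. The change should be made before unblinding.

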**Primary outcomes:**

Respiratory muscle strength, dyspnea, and quality of life of post-COVID-19 patients.

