### Inclusion criteria

Sedentary patients of both genders, diagnosed with COVID-19 using reverse transcription polymerase chain reaction, aged above 18 years, without other respiratory diseases associated or cardiac disease, with adequate cognitive capacity (Mini-Mental State Examination [MMSE]), and reduced respiratory muscle strength will be included. Reduced inspiratory muscle strength will be defined using MIP [14].

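### Within-arm Wilcoxon tests are planned as outcome comparisons beside the sham comparison, in patients selected for low MIP who may improve without any training effect

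*Protocol article*

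**What the plan says.** The Primary objective is a between-arm question: home-based training is "compared to an IMT SHAM group for improving respiratory muscle strength, dyspnea, and quality of life". The primary outcomes are "Respiratory muscle strength, dyspnea, and quality of life of post-COVID-19 patients".

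The Statistical analysis section, repeated in the Abstract, has two branches. In the non-normal branch, outcomes are to be compared by "Wilcoxon (intragroup analysis) and Mann-Whitney test (intergroup analysis". In the other branch, "repeated measures two-way ANOVA will be performed in case of parametric distribution". Neither branch names the test or ANOVA effect on which effectiveness is judged.

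Under Inclusion criteria, only patients with "reduced respiratory muscle strength will be included", and "Reduced inspiratory muscle strength will be defined using MIP". No numerical cut-off appears in the article. MIP is also the sizing variable (Type of study and location of research) and is part of the first primary outcome (Respiratory muscle strength). The Interventions section describes one pre-training evaluation, then "post-training (six weeks after pre-training), and retention (24 weeks after pre-training". No second measurement between screening and baseline is described.

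The Intervention protocol section says that sham patients will be invited to train with load if the active treatment proves effective. It does not say which result settles that.

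**The concern.** A before-after test in one arm asks whether that arm changed, not whether training changed it more than sham did. Two things other than training can move an arm here.

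- **Regression to the mean.** Patients enter because their MIP is low. If the qualifying value also serves as baseline, and MIP is not perfectly repeatable, the next value is expected to be higher in both arms. This acts directly on MIP. It reaches dyspnea and quality of life only through their correlation with MIP.
- **Recovery.** These are post-COVID patients followed to 24 weeks. Spontaneous improvement in MIP, dyspnea and quality of life is plausible in both arms.

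The non-normal branch is likely to be used for at least one primary outcome, because dyspnea is scored on a five-point scale. The within-arm tests stand in the same sentence as the between-arm test, with nothing to rank them. A report could then cite a significant active-arm change, or significance in one arm only, as evidence of efficacy. The offer of loaded training to sham patients depends on the same undefined judgement.

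**Working it through.** The article states no sample size, effect size, MIP cut-off or test-retest reliability, so there is no figure of its own to reproduce. What follows is conditional.

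**Assumed inputs.**
- Selection: lowest 30% or lowest 50% of MIP.
- Test-retest correlation r: 0.80 to 0.95.
- Analysed patients: 20 per arm. The plan's two-sided 5% level and 80% power would give 16 per arm for a standardised difference of 1.0 and 25 for 0.8, so 20 lies between.
- Identical arms, no training effect.

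**Expected shift from selection alone.** With q the selected fraction and c its normal cut-off, the shift in population SD is (1 − r) × φ(c)/q.
- Lowest 30%: φ(c)/q = 1.159. For r = 0.85 the shift is 0.15 × 1.159 = 0.17; for r = 0.90 it is 0.12; for r = 0.80 it is 0.23.
- Lowest 50%: φ(0)/0.5 = 0.798. For r = 0.95 the shift is 0.05 × 0.798 = 0.04; for r = 0.80 it is 0.16.

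**Simulation.** Baseline is drawn from the selected part of a standard normal. Follow-up is r × baseline plus normal noise with variance 1 − r². The Wilcoxon test is run in each arm and Mann-Whitney between arms, at 5% two-sided.

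| Selection | r | Shift (SD) | Arms significant | Active significant, sham not |
|---|---|---|---|---|
| Lowest 30% | 0.80 | 0.23 | 35% | 22% |
| Lowest 30% | 0.85 | 0.17 | 27% | 19% |
| Lowest 30% | 0.90 | 0.12 | 20% | 16% |
| Lowest 50% | 0.80 | 0.16 | 18% | 15% |
| Lowest 50% | 0.85 | 0.12 | 13% | 12% |
| Lowest 50% | 0.90 | 0.08 | 10% | 8% |
| Lowest 50% | 0.95 | 0.04 | 8% | 7% |

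Simulation error is one to two percentage points. The arms are independent, so the last column should be close to p(1 − p), where p is the column before it: 0.27 × 0.73 = 20%. The last row is taken this way: 0.08 × 0.92 = 7%.

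**Benchmarks.** An unbiased within-arm test would be significant in 5% of arms and give the discordant pattern in 0.05 × 0.95 = 4.75% of trials. Mann-Whitney stays at about 5% over both directions, so about 2.5% in favour of active. Over a wider grid of cut-offs, reliabilities and sample sizes it ran from 3.8% to 5.8% on post-training values and from 3.6% to 6.0% on changes.

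**Outside the table.** With the lowest 30% and 30 per arm, 28% to 50% of arms are significant. With a cut-off at −1 SD and r = 0.80, the figure is 44% at 16 per arm and 87% at 40. The table is therefore not an upper bound.

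**Adding recovery.** With 0.3 population SD of recovery in both arms, the lowest 30% and 20 per arm, about 95% to 96% of arms are significant. The discordant pattern then falls to about 4% (0.96 × 0.04 = 3.8%), and Mann-Whitney stays at about 5%. Without selection, recovery of 0.3 or 0.5 SD of the change makes the within-arm test significant in 32% or 67% of arms at 26 per arm. That case is the closer one for dyspnea and quality of life.

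**The case against.** The strongest reply is that the sham control is in use. The trial is randomised and blinded, its objective names sham, and the sentence that plans the Wilcoxon test also plans the Mann-Whitney test. Nowhere does the article say that efficacy will be concluded from a within-arm p-value. Choosing the confirmatory contrast is work that a full protocol or analysis plan often does, and within-arm p-values printed beside a between-arm test do not invalidate it.

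Most of this stands. A reader might infer that the randomised comparison is bypassed; the article does not support that. A reader might also infer that every arm will appear to improve. Under selection alone, most arms do not in any scenario tabulated above, and the figure falls to 8% in the mildest. A reader might further infer three unadjusted Wilcoxon tests per arm, with a family-wise error of up to 1 − 0.95³ = 14%. The article names no visit pairs and does not rule out adjustment, and that figure assumes independent tests although the pairs share visits.

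Recovery cuts both ways. It makes nearly every arm significant, but then sham is visibly significant too, which warns the reader that the change is not specific to training. In the normal branch, the repeated measures ANOVA contains a valid group-by-time test.

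What does not fall away is that the within-arm tests are written into the plan as outcome comparisons. That is a stated choice, so it is more than a missing detail.

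**Conclusion.** The point holds as a defect of analysis choice that should be corrected, not as one that leaves the trial without a valid test. A within-arm Wilcoxon test cannot answer the stated question. In patients chosen for low MIP it is biased towards finding improvement in MIP whenever the qualifying measurement serves as baseline and MIP is less than perfectly repeatable. The direction of that bias is firm; its size is not. With 20 per arm and no true change, roughly 8% to 35% of arms reach significance, and roughly 7% to 22% of null trials show active significant and sham not. The low end is the lowest 50% with r = 0.95, and the high end is the lowest 30% with r = 0.80. Stricter selection or larger arms raise the within-arm figure, and a separate baseline after screening would lower it. All of this rests on an assumed cut-off, reliability and sample size. Whatever their values, significance in one arm and not in the other is not a test of active against sham.

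**What to change.** In the Statistical analysis section and the matching text of the Abstract:

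- State that efficacy is concluded only from active versus sham: Mann-Whitney on change from baseline in the non-normal branch, and the group-by-time effect in the ANOVA branch.
- Drop the intragroup Wilcoxon tests as outcome comparisons. Report within-arm change descriptively, as median or mean change with a 95% confidence interval, and say that no efficacy claim follows from change in one arm.
- Say that the reference to effectiveness in the Intervention protocol section means the result of that between-arm comparison.

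This is a change of wording only. It needs no new patients, visits or measurements. The price is that fewer p-values are reported.

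### The three-visit ANOVA ties the active-versus-sham question to no term or visit: for MIP alone, null error is about 10% if either between-arm term may count, and power depends on the term read

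*Protocol article*

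**What the plan says.** All references are to the Protocol article.

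- **Statistical analysis:** for normally distributed variables, "repeated measures two-way ANOVA will be performed in case of parametric distribution", and "Dunn’s post hoc test will be used to identify significant differences in the two-way ANOVA test". Otherwise, "Variables presenting nonparametric distribution will be compared using Wilcoxon (intragroup analysis) and Mann-Whitney test (intergroup analysis"). The level is set by "A significance level of 5% will be applied to minimize type I error".
- **Interventions:** the visits are "pre-training (initial), post-training (six weeks after pre-training), and retention (24 weeks after pre-training"). The Abstract (Methods and analyses) puts the post-training visit at three weeks.
- **Type of study and location of research:** "Sample size will be determined using maximal inspiratory pressure (MIP") after a pilot with five patients per group, and "a bilateral distribution with alpha error of 0.05 and 80% power will be adopted". Neither the visit nor the scale (value or change) of that MIP effect is given.
- **Primary objective:** the question is training compared with sham, so it is a between-arm question.

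**The concern.** Two arms and three visits give three F tests (group, time, group-by-time) plus post hoc comparisons. Two of the three F tests compare the arms, and they ask different questions.

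- The **group** term averages all three visits, including pre-training, where randomised arms have no systematic difference. That dilutes any effect.
- The **group-by-time** term has two degrees of freedom and asks whether the arm difference changes in any way over the visits. It does not isolate the end of training.

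The article sizes the trial on one MIP effect but does not say which of these tests that effect belongs to. Two things follow. If either term may support a claim, the 5% level no longer describes the error rate, even for MIP alone. And the planned 80% power need not apply to the test that is finally read. This is separate from the number of primary outcomes.

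**Working it through.** **Inputs from the article:** two parallel arms, three visits, two-sided 5%, 80% power, 20% dropout. It states no sample size, effect size, SD or correlation, so there is no figure of its own to reproduce.

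**Assumptions:** effect 0.8 SD of a single-visit MIP value at the post-training visit; equal allocation; normal complete data; equal variances; equal correlation ρ between visits, 0.3 to 0.7. The effect at 24 weeks is sustained (0.8), half faded (0.4) or gone (0).

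**1. Planning size.** Two-sample t test, noncentrality d√(n/2). With n = 26: 0.8 × √13 = 2.88 on 50 df, power 81% (25 per arm gives 79%). With dropout, 52 / 0.8 = 65 in total. For d = 0.5, 1.0 and 1.2 the size would be 64, 17 and 12 per arm.

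**2. Null error if group or group-by-time may count.** Under these assumptions the two tests are nearly independent: 1 − 0.95² = 9.75%. Simulation gives 9.5 to 10.0%. If unadjusted arm comparisons at each follow-up visit may also count, it is 12.5 to 14.3%.

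**3. Group term.** Standardised effect = (mean of the three arm differences) / √((1 + 2ρ)/3). Sustained, ρ = 0.5: (0 + 0.8 + 0.8)/3 = 0.533; divided by √(2/3) = 0.816, this is 0.653. Noncentrality 0.653 × √13 = 2.36, power 64%. With a sustained effect the group term matches the plan when (2/3)/√((1 + 2ρ)/3) = 1, that is at ρ = 1/6; above that it loses power.

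**4. Group-by-time term.** λ = (n/2) × Σ(difference − mean difference)² / (1 − ρ), F on 2 and 100 df. At ρ = 0.5:
- Sustained: squared deviations sum to 0.427, λ = 13 × 0.427 / 0.5 = 11.1, power 84%. An effect gone by week 24 gives the same sum.
- Half faded: sum 0.32, λ = 8.32, power 72%.

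**5. Post-training contrast adjusted for pre-training MIP.** Residual SD √(1 − ρ²). At ρ = 0.5: 0.8 / 0.866 = 0.924, noncentrality 3.33 on 49 df, power 90%. Its simulated null error is 4.8 to 5.1%.

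| ρ | Group: sustained / half faded / gone | Group-by-time: sustained or gone / half faded | Adjusted post-training contrast |
|---|---|---|---|
| 0.3 | 73 / 49 / 25% | 70 / 57% | 84% |
| 0.5 | 64 / 41 / 21% | 84 / 72% | 90% |
| 0.7 | 56 / 35 / 18% | 97 / 92% | 97% |

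The last column is simulated; the others come from the formulas. Separate simulations of group-by-time gave 56 to 69%, 74 to 85% and 92 to 98% at the three correlations, and 83% for the adjusted contrast at ρ = 0.3.

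**6. If the 0.8 is in SDs of change instead.** Group-by-time has 84% (sustained or gone) or 72% (half faded) at any ρ. The group term with a sustained effect has 86, 64 and 37% at ρ = 0.3, 0.5 and 0.7.

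**The case against.** - **This is detail for a statistical analysis plan.** A condensed article may leave the deciding term and visit to a document that is not shown. That stands against treating the silence itself as the finding. What remains is that the article does fix a method, one that treats the pre-training visit as an outcome, and sizes the trial on a single effect without linking the two. A better test is available from the same data.
- **The post hoc step may control the error.** Dunn's is a multiple-comparison procedure. With a Bonferroni-type adjustment over the two follow-up visits, simulated error is 4.1 to 5.0% without gating, about 3.3% if gated on group or group-by-time, and 0.6 to 1.4% if gated on group-by-time. This stands: the 10% is conditional on letting either between-arm term count. The article fixes neither sequence.
- **The visits have labels.** Post-training and retention are not presented as interchangeable. This is fair, and the fix uses those labels, but neither is named as deciding.
- **The group-by-time term can be adequate.** At ρ of 0.5 or more it exceeds 80% when the effect is sustained or gone by week 24. This stands. Even so, the adjusted contrast is at least as powerful in every case in the table.

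**Conclusion.** The point holds in a limited form. The parametric analysis leaves open which between-arm test answers the trial's question. If either group or group-by-time may count, null error for MIP alone is about 10%. The group term usually loses power against the plan. The group-by-time term can, depending on correlation and fading. The powers rest on the assumed effect of 0.8, 26 per arm and equal correlation between visits.

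A reader might infer three stronger things that the article does not support:

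- **That a significant time term would count as success.** Recovery in both arms would indeed make that term significant (88 to 99.9% of simulated trials with 0.5 SD recovery and no treatment effect). But the Primary objective sets a comparison with sham, and no sentence makes the time term the treatment test.
- **That the tests are underpowered as a matter of fact.** With no effect size, SD, correlation or sample size stated, this can only be conditional.
- **That the two follow-up visits would often give opposite verdicts.** That frequency depends on how far the effect is assumed to fade, on which the article is silent.

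**What to change.** In Statistical analysis, state that the treatment test for MIP is the active-minus-sham difference at the post-training visit, adjusted for pre-training MIP (ANCOVA, or that contrast from a mixed model with baseline as covariate), two-sided 5%. Make the retention visit secondary. Report the group and time main effects and within-arm changes descriptively. Use the same form for the other continuous outcomes.

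In the sample size paragraph, base the calculation on this contrast and name its visit and scale.

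Reconcile the timing of the post-training visit between the Abstract (three weeks) and Interventions (six weeks), so that the named visit is unambiguous.

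How the three primary domains (respiratory muscle strength, dyspnea, quality of life) are combined is a separate question that this change does not settle.

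The cost is wording; no new data or visits are needed. The downside is that a difference seen only at 24 weeks, or only in another ANOVA term, could not be claimed as the main MIP result.

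### Dunn's test is named as the follow-up to a repeated measures ANOVA that it does not fit: read literally, within-arm visit contrasts lose power, while active-versus-sham contrasts lose little

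*Protocol article*

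**What the plan says.** The section Statistical analysis splits outcomes by a normality check. Non-normal variables are "compared using Wilcoxon (intragroup analysis) and Mann-Whitney test (intergroup analysis"). For the others, "repeated measures two-way ANOVA will be performed in case of parametric distribution". The next sentence names Dunn's test as the follow-up to that parametric model: it is the "post hoc test will be used to identify significant differences in the two-way ANOVA test". The abstract repeats this, so a stray word in one place is unlikely.

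The design is a "randomized, controlled, double-blind, parallel, two arm clinical trial" (Type of study and location of research). Patients are assessed at "pre-training (initial), post-training (six weeks after pre-training), and retention (24 weeks after pre-training") (Interventions). The ANOVA therefore has two groups and three correlated visits per patient.

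**The concern.** Dunn's test normally follows a rank-based omnibus test on independent groups. Here it is attached to the normal-theory branch and to repeated measurements on the same patients. Done literally, it replaces the ANOVA's means with pooled ranks and the ANOVA's within-patient error term with a variance that treats the visits as separate samples. An analyst following the text would report follow-up p-values that do not come from the model they are meant to explain.

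What is at stake is mainly the change from one visit to another within an arm. The plan does intend within-group comparisons, since it names an intragroup test in the nonparametric branch. The mismatch could touch any outcome that passes the normality check, possibly including maximal inspiratory pressure, the variable that sets the sample size.

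**Working it through.** **Inputs from the protocol.** Two parallel arms, three visits, 5% significance level. For the sample size, "a bilateral distribution with alpha error of 0.05 and 80% power will be adopted". The protocol states no N, SD, effect size or within-patient correlation (ρ). It leaves the effect to a pilot of five patients per group, where "Mean and standard deviation will be used to estimate effect size". There is therefore no stated figure to reproduce.

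**Assumed inputs.** Normal data, equal correlation ρ between visits, and three Bonferroni-adjusted contrasts (two-sided 0.05/3 = 1.7% each, critical z = 2.394). Three settings are used:
- 25 per arm at 0.8 SD and 63 per arm at 0.5 SD. Both give about 80% power for a two-sided 5% comparison of two means. Active means are 0, d, d and sham means are flat; 2,000 simulated trials per value of ρ.
- 30 patients in one arm, with a shift of 0.5 SD between two visits; 4,000 simulated data sets. At 0.5 SD, 30 per arm gives only 48% power between arms, so this setting falls short of the plan's own power target.

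**Step 1: where the pairing is lost.** For n patients and SD σ, the variance of a visit-to-visit mean difference is 2σ²(1−ρ)/n. Dunn's variance, N(N+1)/12 × (1/nᵢ + 1/nⱼ), has no covariance term and corresponds to 2σ²/n. Its z statistic then has SD of about √(1−ρ) instead of 1.

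**Step 2: no true change.** The rejection rate is about 2[1 − Φ(2.394/√(1−ρ))]. At ρ = 0.5 this is 2[1 − Φ(3.39)], about 0.1%. At ρ = 0.7 it is 2[1 − Φ(4.37)], practically 0. Simulation gives 0.1% and 0%, against the intended 1.7%. The test is conservative.

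**Step 3: true change.** Dunn's expected z is about d√(n/2) × √(3/π), with √(3/π) = 0.977.
- n = 30, d = 0.5: 0.5 × 3.873 × 0.977 = 1.89, below 2.394. Power falls as ρ rises: Φ[(1.89 − 2.394)/0.707] ≈ 24% at ρ = 0.5, and Φ[(1.89 − 2.394)/0.548] ≈ 18% at ρ = 0.7.
- n = 25, d = 0.8: 0.8 × 3.536 × 0.977 = 2.76, above 2.394. Power does not fall as ρ rises, but it still lags behind the paired contrast.

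This is why the size of the loss depends so strongly on the assumed N and effect.

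**Step 4: simulated power, pre- versus post-training within the active arm**

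| n, effect | ρ | Paired t, Bonferroni | Dunn, visits as independent groups | Loss (points) |
|---|---|---|---|---|
| 25, 0.8 | 0 | 59.0% | 59.3% | 0 |
| | 0.3 | 79.2% | 63.5% | 16 |
| | 0.5 | 92.2% | 64.7% | 28 |
| | 0.7 | 99.1% | 66.8% | 32 |
| | 0.9 | 100% | 76.1% | 24 |
| 63, 0.5 | 0 | 64.3% | 62.8% | 2 |
| | 0.3 | 80.6% | 64.6% | 16 |
| | 0.5 | 92.9% | 67.2% | 26 |
| | 0.7 | 99.6% | 68.8% | 31 |
| | 0.9 | 100% | 81.8% | 18 |
| 30, 0.5 | 0.5 | 58% | 23% | 35 |
| | 0.7 | 83% | 18% | 65 |
| | 0.8 | 96% | 17% | 79 |

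**Step 5: active versus sham at post-training.** These are different patients, so there is no pairing to lose. With the same three-fold adjustment on both sides, the two-sample t has 61–67% power and Dunn's test over the six group-by-visit cells has 60–64%. Setting by setting the gap is 1.6 to 4.0 points, at every ρ from 0 to 0.9. With two contrasts and 30 per arm at 0.5 SD, the figures are 37–38% against 34–36%.

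**The case against.** **The name is ambiguous.** Dunn's name also belongs to the Bonferroni-type comparison of means, which fits an ANOVA. A Dunn-type contrast on within-patient ranks also keeps the pairing: its power is 83% at ρ = 0.5 and 95% at ρ = 0.7 in the 25-patient, 0.8 SD setting. The protocol never says that visits will be treated as independent samples. This objection stands: the loss in the table is what the literal reading costs, and it is not certain to occur. But a reader cannot tell which procedure is meant, and the usual meaning is the one that does not fit.

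**A reader might infer that the follow-up contrasts in general lose most of their power.** The documents do not support that. The loss is confined to contrasts between visits within an arm, it needs a correlation that the protocol does not state, and it exceeds half the power only in the smaller, underpowered setting. The treatment comparison at a visit is nearly untouched.

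**A reader might also infer that the arm difference at post-training is not addressed at all.** Even the literal rank test over the six cells includes that pair, though it compares mean ranks and not means.

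**Family size.** Six cells give 15 pairs. If all 15 were adjusted for, Dunn's power for active versus sham at post-training would be 36–38%, against 69–70% for a t contrast limited to the two post-baseline visits (25 per arm, 0.8 SD). That gap comes almost wholly from the size of the family, since Dunn's test limited to two contrasts gives 66–69%. The protocol does not say that all 15 pairs will be tested. A condensed article may leave the list of contrasts, and any multiplicity rule for the nonparametric branch, to a statistical analysis plan, so neither is counted here.

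**Conclusion.** The point holds as a specification error of modest weight. The plan states a follow-up procedure that, in its usual sense, does not belong to the model it is attached to. On that reading, within-arm visit contrasts are conservative and lose about 0 points of power at correlation 0, about 16 at 0.3, and about 25 to 65 at 0.5 to 0.7. The upper end comes from 30 patients with a 0.5 SD change, and sizes matched to 80% power give 26 to 32. Active versus sham at a visit loses about 2 to 4 points. The group-by-time F test does not depend on the post hoc choice.

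All of these figures rest on assumed N, effect and correlation. The mismatch between test and model rests on the text alone; whether it does harm depends on which Dunn procedure is run.

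**What to change.** In Statistical analysis and in the abstract, replace Dunn's test with Bonferroni- or Holm-adjusted contrasts of the estimated marginal means from the same repeated measures model. Name active versus sham at the post-training and 24-week visits as the contrasts of interest, and report each with its 95% confidence interval. If the Bonferroni-Dunn adjustment on means was intended, name it as such and tie it to those contrasts.

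The cost is one sentence in each place. The SPSS version already named offers the adjustment, and no new data, visits or patients are needed.
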